**Ethical approval**

This project will be conducted with ethical approvals from the Stockholm Ethics Review Board (2014/1287-31/4, 2018/972-32, and 2022-05774-02).

*Non-prespecified Analysis (Analysis according to comments from external reviewers):*

- Assess the association between statin use and risk of left-sided or right-sided colon cancer;
- Assess the association between statin use and cancer stage (measured by TNM classification and categorized into two groups: I-II or III-IV);
- To assess the robustness of our results, we added one sensitivity analysis by excluding individuals with a history of diabetes before statin initiation.

| Table 1. International Classification of Disease (ICD) codes and SNOMED codes for defining IBD | | | | | |
| --- | --- | --- | --- | --- | --- |
| IBD subtypes ^a^ | ICD-7 (1964-1968) | ICD-8 (1969-1986) | ICD-9 (1987-1996) | ICD-10 (1997-) | SNOMED codes ^b^ |
| Ulcerative colitis (UC) | 572,20; 572,21; 578,03 | 563,1; 563,10; 569,02; 569,04 | 556 | K51 | D6255 or M41, M42, M43, M44, M463, or M47 |
| Crohn's disease (CD) | 572,00; 572,09 | 563,00 | 555 | K50 | D6216 or M41, M42, M43, M44, M463, or M47 |
| IBD unclassified (IBD-U) | UC + CD | UC + CD or 563; 563,0; 563,9; 563,98; 563,99 | UC + CD | UC + CD or K52.3 | D6214 or M41, M42, M43, M44, M463, or M47 |
| ^a^ Subtypes of IBD were defined according to the first two diagnostic codes only, therefore no information after start of follow-up contributed to such definition; and the IBD subtype was only determined by the ICD code if one individual had one ICD code for IBD and one M code. ≥1 ICD code for IBD plus a relevant biopsy code has a positive predictive value of 95% ^9,16^. In a recent paper ^17^, we report that 18% of incident IBD patients in the Swedish patient register during 2002-2014 were classified as another IBD subtype at some point during follow-up. | | | | | |
| ^b^ SNOMED codes starting with M (inflammation suggestive of IBD, but not a specified subtype) were required to be accompanied by a topographic code of T67 or T68 (colon); for example, M41 refers to all codes starting with M41; D codes are diagnostic codes but listed under morphology in pathology registers; D6255, for example, is the diagnostic code for UC. | | | | | |

| Table 2. Definitions of statin, outcomes, exclusion criteria, comorbidities, and medications | |
| --- | --- |
| Statin | **ATC code** ^a^ |
| Simvastatin | C10AA01 |
| Pravastatin | C10AA03 |
| Atorvastatin | C10AA05 |
| Rosuvastatin | C10AA07 |
| **Outcomes** | **ICD code** ^a^ |
| Incident colorectal cancer (CRC) ^b^ | ICD-7: 153-154, but not 1541 (anal cancer) or 1534 (appendiceal cancer) |
| CRC-related mortality | ICD-10: C18-20, but not C181 (appendiceal cancer) |
| All-cause mortality | ICD-10: A00-U99 |
| **Proctocolectomy and colectomy** | **Procedure code** |
| Proctocolectomy ^c^ |  |
|  | Sixth version (1969-1996): 4652, 4653, 4654 |
|  | Seventh version (1997-): JFH20-JFH40 |
| Colectomy with an intact rectum ^d^ |  |
|  | Sixth version (1969-1996): 4650, 4651 |
|  | Seventh version (1997-): JFH00, JFH01, JFH10, JFH11, JFH96 |
| Rectum amputation after a colectomy with an intact rectum ^e^ |  |
|  | Sixth version (1969-1996): 4820, 4821, 4822, 4828 |
|  | Seventh version (1997-): JGB00-JGB97 |
| **Exclusion criteria** | **ICD-10 code/procedure code** |
| Cancer | C00-C97, except non-melanoma skin cancer (C44) |
| HIV/AIDS | B20-B24, F024, O987, R75, Z114, Z219, Z711 |
| Primary immunodeficiency disease | D71, D80–D84 |
| Severe liver failure | B150, B160, B162, B190, K704, K72, K766, I85 |
| End-stage renal disease | N18.5,  N18.6, Z49, Z99.2, Z94.0; Procedure codes: 9200; V9200; 9212; V9212; 9314; V9531; DR012; DR013; DR016; DR024; QF006; 9211; V9211; 9213; V9213; V9532; DR015; DR023; DR055; DV056; 9219; V9219; 9223; V9223; DR017; DR020; DR055; DR056; 6070; KAS10; KAS20 |
| Any organ transplantation | Swedish surgery codes (KVÅ codes): KAS, FQA, FQB, GDG, JJC |
| **Comorbidities** | **ICD-10 code** |
| Gastrointestinal diseases | K00-K99 |
| Intestinal infections | A00-A09 |
| Cardiovascular diseases | I00-I99 |
| Obesity/dyslipidemia | E78 , E65, E66 |
| Type 1 and type 2 diabetes | E10-E14 , O24 |
| Autoimmune diseases | E035, E039, E050, E055, E059, E063, E065, G35, M05-M09, M32, L40 |
| Obstructive sleep apnea | G473 |
| Chronic obstructive pulmonary disease (only if diagnosed ≥40 years) | J41-J44 |
| Myositis (no adequate codes present for rhabdomyolysis) | M60 |
| **Medications** | **ATC code** |
| Antibiotics | J01 |
| Proton pump inhibitor | A02BC |
| Antiviral drugs | J05 |
| IBD medications |  |
| Immunomodulators |  |
| Azathioprine | L04AX01 |
| Mercaptopurine | L01BB02 |
| Methotrexate | L04AX03/L01BA01 |
| Anti-TNF treatment |  |
| Infliximab | L04AB02 (L04AA12 before 2008) |
| Adalimumab | L04AB04 (L04AA17 before 2008) |
| Golimumab | L04AB06 |
| Vedolizumab | L04AA33 |
| Systemic corticosteroids |  |
| Betamethasone | H02AB01 |
| Dexamethasone | H02AB02 |
| Methylprednisolone | H02AB04 |
| Prednisolone | H02AB06 |
| Prednisone | H02AB07 |
| Hydrocortisone | H02AB09 |
| Cortisone | H02AB10 |
| Systemic aminosalicylates (5-ASA) |  |
| Sulfasalazine | A07EC01 |
| Mesalazine | A07EC02 |
| Olsalazine | A07EC03 |
| Balsalazide | A07EC04 |
| Rectal aminosalicylates (5-ASA) |  |
| Mesalazine | A07EC02 |
| Corticosteroids acting locally |  |
| Hydrocortisone | A07EA02 |
| Budesonide | A07EA06 |
| Non-aspirin anti-platelet medications | B01AC excluding aspirin (B01AC06) |
| Aspirin | B01AC06 |
| Non-statin lipid lowering medications | C10AB, C10AC, C10AD, C10AX01-14 |
| Anti-diabetic medications | A10 |
| Anticoagulation medications | B01AA, B01AE, B01AF, B01AX |
| Anti-arrhythmias medications | C01BA, C01BB, C01BC, C01BD, C01BG |
| ATC: Anatomical Therapeutic Chemical; CRC: colorectal cancer; HIV/AIDS: human immunodeficiency virus/ acquired immunodeficiency syndrome; ICD: the International Classification of Disease. | |
| ^a^ ATC codes will be identified from the Prescribed Drug Register; ICD codes and procedure codes will be identified from the National Patient Register. | |
| ^b^ Incident CRC will be ascertained from the Cancer Register, while CRC-related mortality will be ascertained from the Cause of Death Register. In the Cancer Register, all ICD-8, ICD-9, and ICD-10 codes were back-translated to ICD-7. | |
| ^c^ Not at risk of colorectal cancer. | |
| ^d^ Only at risk of rectal cancer. | |
| ^e^ Not at risk of colorectal cancer. | |

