**METHOD**

**Data source, study design, and study population**

This cohort study will be based on the nationwide histopathology cohort, Epidemiology Strengthened by histoPathology Reports in Sweden (ESPRESSO)^1^, and several healthcare registers in Sweden. ESPRESSO^1^ contains data on GI-related biopsies from all 28 pathology departments in Sweden from 1965 to 2017. The Total Population Register^2^ contains details on birth, death, and migration, which was initiated in 1968. The Prescribed Drug Register^3^ collects information on medications dispensed at all pharmacies in Sweden since July 2005, including for example dispensing date, drug name, and a defined daily dose (DDD). The National Patient Register^4^ covers data on inpatient (since 1964) and outpatient (since 2001) specialist care with disease diagnoses and surgical procedures. The Cancer Register^5^ contains data from >96% of incident cancer cases since 1958. The Cause of Death Register^6^ contains information on >99% of death since 1952. The Swedish Longitudinal Integrated Database for Health Insurance and Labour Market Studies^7^ contains information on demographic and socioeconomic characteristics (e.g., education and county of residence).

The IBD patients will be identified as those with ≥ 1 biopsy indicating IBD in the ESPRESSO and ≥ 1 International Classification of Disease (ICD) code for IBD in the NPR (see **Table 1** for the definition of IBD subtypes)^8^. Such diagnostic approach yields a positive predictive value of 95%^9^.

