**Two-step matching process**

A two-step matching process will be applied to establish the cohort. In the direct matching step, statin users and non-statin users will be matched on age at IBD diagnosis (<18, 18-<40, 40-<60, and ≥60), sex, IBD subtype (CD or UC), and calendar year at IBD diagnosis (1969-1989, 1990-1999, 2000-2009, 2010-2018). IBD-unclassified will not be considered in this project due to diagnostic uncertainty. To ensure similar opportunities for care and treatment^10^, non-statin users should have a random drug prescription (except IBD medications, see **Table 2** for ATC codes) within three months before or after the start date of statin treatment in the matched statin users. All identified non-statin users will be assigned the same index date as the index statin user. We will exclude individuals who had a record of migration, received a colectomy, or had a diagnosis of any of the following diseases before the index date: cancers, human immunodeficiency virus/ acquired immunodeficiency syndrome, primary immunodeficiency disease, end-stage renal disease, severe liver failure, and any organ transplantation (see **Table 2** for procedure and ICD codes).

In the propensity score matching step, statin users and non-statin users will be matched in a 1:1 ratio by using a greedy nearest-neighbor matching algorithm without replacement, with a caliper of 0.2 standard deviation of the logit of the propensity score^11^. A logistic regression model will be used to calculate the propensity score after adjusting for the below demographic and socioeconomic characteristics, comorbidities, and co-medications identified up to and including the index date.

- Age at IBD diagnosis, years (continuous);
- Duration of IBD, years (continuous);
- Number of healthcare visits (continuous);
- Country of birth (Nordic countries or others);
- Education (0-9, 10-12, ≥13 years, or missing);
- Comorbidities (yes/no, see Table 2 for detail): gastrointestinal diseases, intestinal infections, cardiovascular diseases, obesity/dyslipidemia, type 1 and type 2 diabetes, autoimmune diseases, obstructive sleep apnea, chronic obstructive pulmonary disease, and myositis;
- Medications (yes/no, see Table 2 for detail): antibiotics, proton pump inhibitor, antiviral medications, IBD medications, non-aspirin anti-platelet medications, aspirin, non-statin lipid lowering medications, anti-diabetic medications, anticoagulation medications, and anti-arrhythmias medications.

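### Prior cancer is to be excluded without a time limit, but Table 2 defines it by ICD-10 codes alone, so a cancer recorded before 1997 and not coded again before index stays in the cohort

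*SAP*

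**What the plan says.** The rule is in the SAP section Two-step matching process. It removes anyone who "had a diagnosis of any of the following diseases before the index date: cancers", followed by other conditions. No start date is attached.

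The definition is in Table 2, in the exclusion block headed "ICD-10 code/procedure code". The cancer row reads "C00-C97, except non-melanoma skin cancer (C44". It gives no ICD-7, ICD-8 or ICD-9 codes.

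On sources, footnote a to Table 2 says that "ICD codes and procedure codes will be identified from the National Patient Register". Footnote b says that "Incident CRC will be ascertained from the Cancer Register" and adds: "In the Cancer Register, all ICD-8, ICD-9, and ICD-10 codes were back-translated to ICD-7".

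On coverage, the section on data source, design and population says that the Patient Register "covers data on inpatient (since 1964) and outpatient (since 2001) specialist care", and that the Cancer Register "contains data from >96% of incident cancer cases since 1958". Table 1 dates ICD-10 from 1997.

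**The concern.** The exclusion is meant to leave a cohort free of cancer at index. The code list that carries it out begins in 1997, whereas IBD diagnoses are accepted from 1969 and the rule has no time limit. Other parts of the SAP do reach further back: Table 1 gives ICD-7 to ICD-9 codes for IBD, and the colectomy and proctocolectomy rows of Table 2 give procedure codes for 1969-1996. Prior cancer, the exclusion closest to the primary outcome, has no code from before 1997.

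Three things are at stake. A CRC survivor left in the cohort could contribute a later CRC record to an outcome described as incident. The same person could contribute a CRC-coded death to the first secondary outcome. A survivor of any cancer would contribute to all-cause mortality. Nothing later in the plan makes up for this: prior cancer is not among the propensity-score covariates, and no sensitivity analysis addresses it. Discarding the first one or two years of follow-up removes early events, not people with an old cancer.

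**Working it through.** The SAP states no figure on this point to reproduce. The check is calendar arithmetic and a comparison of the relevant sections.

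**Inputs**
- Start of ICD-10: 1997 (Table 1).
- Outpatient data in the Patient Register: from 2001; inpatient data from 1964 (data source section).
- Cancer Register: from 1958 (data source section).
- Earliest index date: July 2006, taken as 2006.5 (Identification of statin users).
- End of follow-up: December 2019, taken as 2020.0 (Identification of primary and secondary outcomes).

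**Look-back = index date minus start of usable coding**

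| Search | Calculation | Years before index |
| --- | --- | --- |
| ICD-10 list, earliest index | 2006.5 − 1997.0 | about 9.5 |
| of which with outpatient data | 2006.5 − 2001.0 | about 5.5 |
| ICD-10 list, latest conceivable index | 2020.0 − 1997.0 | at most about 23 |
| Cancer Register, earliest index | 2006.5 − 1958.0 | about 48.5 |

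The Cancer Register years outside the ICD-10 period are 1958 to 1996: 1996 − 1958 + 1 = 39, which agrees with 48.5 − 9.5 = 39. This counts register years, not patients.

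**Does the choice of register change the result?**
1. If the cancer row is searched in the Patient Register, as footnote a suggests, a cancer coded only in 1996 or earlier carries a pre-ICD-10 code and is not found.
2. If the row is searched in the Cancer Register instead, the codes there are ICD-7 (footnote b), and C00-C97 does not match them. The SAP itself switches to ICD-7 153-154 for the CRC outcome in that register.

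The list as printed does not deliver the stated exclusion on either reading.

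**Who is missed?** A person is retained only if all of the following hold: the cancer was recorded before 1997, it was not given a C-code between 1997 and index, and no other exclusion applies. A pre-1997 cancer that is coded again in care from 1997 onwards is caught.

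**The case against.** Five counter-arguments deserve weight.

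*The window is already long.* Every patient has at least about 9.5 years of ICD-10 coding before index, and some have over 20. An old cancer still under care would probably be coded again. This stands as a limit: the gap concerns only cancers with no later code, and it would be wrong to infer that all pre-1997 cancers are retained.

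*Earlier CRC is partly covered.* Colectomy before index is an exclusion and has codes for 1969-1996. The outcome section also ends follow-up at the earliest recorded date of incident CRC, and the register used for it goes back to 1958. Read literally, someone with a CRC in 1985 has that date before index, so a later tumour is not the first record. This stands in part, and a reader who infers that the primary endpoint is not incident goes further than the text allows. The colectomy route, however, misses anyone treated without a listed procedure. The outcome wording is a follow-up rule: it does not say what happens to a person whose first record precedes index, and it covers neither CRC deaths nor other cancers.

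*The source register is inferred.* The superscript for footnote a is printed on the statin and outcome headers, not on the exclusion header. Footnote b also overrides footnote a for the outcomes, so footnote a is not exhaustive. On the other side, footnote a mentions procedure codes, which appear only in blocks without the superscript, so it seems meant to reach them. The source is best called apparent rather than fixed. As shown in the working, the gap does not depend on it.

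*The same list applies to both groups.* Statin users and non-users face identical exclusion codes, and the SAP gives no basis for saying that misclassification differs between them. This stands: no direction of bias in the hazard ratio can be claimed.

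*The subgroup of long IBD duration.* A reader might infer that patients with IBD for ten years or more are affected most. The gap depends on when the cancer occurred, not on when IBD began. Someone diagnosed with IBD in 2012 can have an unrecorded 1985 cancer. The SAP does not support the inference.

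**Conclusion.** The point holds in a limited form. The text excludes any cancer before index, but Table 2 can detect only cancers coded in ICD-10, that is, from 1997. A cancer recorded earlier and not coded again by index is not excluded. At the earliest index date the look-back is about 9.5 years, against about 48.5 available in the Cancer Register.

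This rests on the 1997 start of ICD-10 in Table 1 and on using the code list as printed. It does not depend on which register is searched.

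The SAP gives no share of patients affected, no excess risk for those retained and no direction of bias, and none can be derived from it. The number is probably small, which is a judgement and not a calculation. The point matters because the rule fails its own criterion and the remedy is cheap, not because a material distortion of the results has been shown.

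**What to change.** In Table 2, define prior cancer as any Cancer Register record from 1958 to the index date, using ICD-7 codes and leaving out non-melanoma skin cancer. Supplement it with Patient Register codes in the earlier ICD versions and in ICD-10. Name the source registers and the look-back in that row, so that they do not hang on a footnote not marked on the block.

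In the outcome section, state that incident CRC is the first-ever CRC record in the Cancer Register, and that anyone whose first record falls before index is excluded.

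The cost is a revised code list and the loss of a few patients. No new data source is needed, since the SAP already draws on the Cancer Register for the primary outcome.

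### Two propensity-score comorbidity flags are coded too broadly: the gastrointestinal flag contains the cohort's own IBD codes, and obesity is pooled with dyslipidemia, so the planned balance check can miss imbalance in what they contain

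*SAP*

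**What the plan says.** The section on the two-step matching process puts comorbidities into the logistic propensity model as binary indicators: "Comorbidities (yes/no, see Table 2 for detail): gastrointestinal diseases", followed by the other conditions. They are counted up to and including the index date. The same section calls a covariate well balanced when its SMD is below 10%.

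The Comorbidities block of Table 2 gives the codes, in ICD-10 only. Two rows matter here: "Gastrointestinal diseases | K00-K99" and "Obesity/dyslipidemia | E78 , E65, E66". Neither carries an exclusion or a split.

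Table 1 gives the cohort-defining codes. The ulcerative colitis row ends "563,1; 563,10; 569,02; 569,04 | 556 | K51" and the Crohn's disease row reads "572,00; 572,09 | 563,00 | 555 | K50". Cohort entry requires a biopsy and at least one "International Classification of Disease (ICD) code for IBD in the NPR". Note a to Table 2 names the source for the diagnosis codes: "ICD codes and procedure codes will be identified from the National Patient Register".

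**The concern.** A yes/no covariate helps a propensity model only if it separates patients on something that matters.

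The gastrointestinal flag is set by the diagnosis that brought the patient into the study. It therefore says almost nothing about other digestive disease. No other comorbidity row in Table 2 contains a K code, so that disease would go essentially unadjusted.

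The obesity/dyslipidemia flag joins two conditions that are likely to relate differently to treatment. Dyslipidemia is a reason to start a statin and should be commoner in users. Obesity need not be. Matching on the union can then pair a dyslipidemic user with an obese non-user, and both count as yes.

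In both cases the SMD is judged on the variable as coded, so the check can report good balance while the component conditions differ. At stake is the control of confounding in the main analysis of colorectal cancer and mortality.

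**Working it through.** The SAP states no figure on this point, so there is none to reproduce. The check has two parts.

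**1. Gastrointestinal flag**

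*Code containment.* K50 and K51 (Table 1) lie inside K00-K99 (Table 2). Both are read from the National Patient Register. ICD-10 runs from 1997 (Table 1) and index dates fall in July 2006 or later, which leaves at least nine calendar years of ICD-10 coding before any index date. A patient whose qualifying IBD code dates from 1997 or later is a yes by construction. An earlier-diagnosed patient becomes a yes at the first K-coded contact after that. A no needs IBD coded only before 1997 and no K code since, so the little variation left reflects era and recency of specialist care.

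*What the SMD check would see.* Let c be the share with a K50/K51 record (the same in both groups) and g the prevalence of any other K code, independent of it.

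- Flag prevalence = 1 − (1 − c)(1 − g)
- SMD = (p1 − p0) / √{[p1(1 − p1) + p0(1 − p0)] / 2}

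Assumed, since the SAP gives no values: g = 50% or 60% in users and 30% in non-users. The true SMD for other K-coded disease is then 0.42 or 0.63.

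| c | Flag, users (g 50% / 60%) | Flag, non-users | SMD of flag |
|---|---|---|---|
| 100% | 100% / 100% | 100% | 0.00 / 0.00 |
| 99% | 99.5% / 99.6% | 99.3% | 0.03 / 0.04 |
| 95% | 97.5% / 98.0% | 96.5% | 0.06 / 0.09 |
| 90% | 95.0% / 96.0% | 93.0% | 0.08 / 0.13 |

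Example: c = 0.99 and g = 0.60 gives 1 − 0.01 × 0.40 = 0.996 in users, and 1 − 0.01 × 0.70 = 0.993 in non-users. These are differences before matching. The flag passes the 10% rule at once in every row except the last at g = 60%.

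**2. Obesity/dyslipidemia flag**

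Let o be obesity (E65/E66) and d be dyslipidemia (E78), independent within each group, with u for users and n for non-users. Suppose matching balances this flag exactly and nothing else.

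- Flag prevalence: F = 1 − (1 − d)(1 − o)
- Obesity in matched non-users: m = F_u × o_n / F_n
- Hazard ratio seen when the truth is 1, approximated by the ratio of mean risks: [1 + o_u(RR − 1)] / [1 + m(RR − 1)]

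Assumed: obesity 5-10% in both groups, E78 in 10-30% of users and 2-5% of non-users, and a risk ratio for obesity of 1.3-1.5. SMDs are users minus matched non-users.

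| Obesity u / n | E78 u / n | F_u / F_n | m | Obesity SMD | Null HR, RR 1.3 / 1.5 |
|---|---|---|---|---|---|
| 5% / 5% | 10% / 5% | 14.5% / 9.75% | 7.4% | −0.10 | 0.993 / 0.988 |
| 5% / 5% | 30% / 2% | 33.5% / 6.9% | 24.3% | −0.57 | 0.946 / 0.914 |
| 10% / 10% | 10% / 5% | 19.0% / 14.5% | 13.1% | −0.10 | 0.991 / 0.985 |
| 10% / 10% | 30% / 2% | 37.0% / 11.8% | 31.4% | −0.55 | 0.941 / 0.908 |
| 10% / 5% | 10% / 5% | 19.0% / 9.75% | 9.7% | +0.01 | 1.001 / 1.001 |
| 10% / 3% | 10% / 5% | 19.0% / 7.85% | 7.3% | +0.10 | 1.008 / 1.013 |

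Worked second row: m = 0.335 × 0.05 / 0.069 = 0.243. With RR 1.5 the null HR is (1 + 0.05 × 0.5) / (1 + 0.243 × 0.5) = 1.025 / 1.121 = 0.914.

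The first four rows give the stated range: obesity 7-31% in matched non-users, SMD about 0.10-0.57, null HR 0.91-0.99. The last two rows start with obesity commoner in users, and there the imbalance disappears or changes sign. If obesity and E78 each have the same prevalence in both groups, F_u = F_n and no imbalance arises. In every row the pooled flag itself has SMD 0.

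**The case against.** On the gastrointestinal flag, the other side can say that everyone in the study has IBD and that subtype is matched directly, so having IBD inside the flag cannot bias the comparison. That is right. A reader might infer that the overlap itself biases the result, but the documents support only lost adjustment. Nor is the flag strictly constant, because cohort strata go back to 1969 and the comorbidity codes are ICD-10 only.

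On obesity, the arithmetic balances one flag alone. The real score also contains diabetes, anti-diabetic drugs, sleep apnea, cardiovascular disease and non-statin lipid-lowering drugs, which may shrink the imbalance. E78 is read from inpatient and specialist outpatient care, so 30% in users is unverified. At the mild end (10% obesity, E78 10% versus 5%) the SMD is 0.097, inside the plan's limit. All of this stands as a limit on size. It does not repair the coding: none of those covariates measures obesity, and no SMD for obesity is planned. The planned exclusions of prior cardiovascular disease and prior diabetes, the E-values and the fracture control do not address either flag directly.

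A reader might extend the point to "Cardiovascular diseases | I00-I99" or to IBD medications. The documents do not carry it that far. The exclusion of prior cardiovascular disease and the separate antiplatelet, aspirin, anticoagulant and anti-arrhythmic flags partly cover the first. For the second, the matching section refers to Table 2, which lists drug classes, so entry by class is a fair reading.

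**Conclusion.** The point holds for two flags. The overlap of K00-K99 with K50/K51 is certain from the text. That the flag is close to constant follows from the dates and registers, although the SAP gives no percentage. The consequence is almost no adjustment for non-IBD digestive disease, and a balance check that can pass regardless.

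For obesity/dyslipidemia the mechanism is certain but its size is not. The range of 0.10 to 0.57 in SMD, and 0.91 to 0.99 for a null hazard ratio, rests on assumed prevalences, equal obesity before matching, independence, balance on this flag alone and an assumed risk ratio. A reader might infer that the pooling must favour statins. The documents do not support that, because the direction depends on prevalences they do not give and it can reverse. The supportable statement is that obesity can be unbalanced without the planned check showing it.

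**What to change.** In the Comorbidities block of Table 2, exclude K50, K51 and K52.3 from the gastrointestinal flag. Replace the pooled obesity/dyslipidemia row with two covariates, E78 and E65/E66. Enter both in the propensity model, and report the SMD before and after matching for each of the three resulting flags.

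The cost is recoding of diagnosis data already drawn from the National Patient Register, one more model term, and possibly a few more statin users left without a match.
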